### Sample size calculation

In a previous study of unemployed patients with spinal cord injury, participants who received IPS were significantly more likely to return to paid employment than those in the CAU group (30.8%; 95% CI 21.8–41.6 versus 10.5%; 95% CI 5.2–19.7, respectively) [25]. Based on these data, a power of 80% and an alpha of 0.05, a total of 148 cancer survivors are required to detect the same difference of 20% between the two groups (nQuery Advisor 7.0). Accounting for a 10% loss to follow-up, we aim to include 164 cancer survivors.

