**Primary outcome measure**			
Paid employment	1	Whether participant has engaged in paid employment since the last questionnaire [yes/no]	Dichotomous

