### Primary outcome measure

The primary outcome measure of this study is paid employment [yes/no] at any point during the 12-month follow-up. Participants will be asked at T1–T3 whether they have worked in paid employment since the previous questionnaire.

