### Effect evaluation

To evaluate the effectiveness of the PLACES intervention compared to CAU at different time points, mixed-effect regression (either linear or logistic regression) with participant as a random intercept will be conducted. Since we stratified for “received social benefit” and the “labor region,” they will be included as covariates in the model. In all models, the main independent variable will be group allocation (i.e., intervention or control group), and both unadjusted and adjusted models will be presented. Additionally, the influence of time (T1, T2, T3) on the intervention’s effect will be examined (group*time interaction effect). The adjusted models will include potential confounders, such as age, gender, time since diagnosis, type of cancer, type of treatment, importance of work, RTW expectation [15, 38], and baseline value of the dependent variable.

In addition, subgroup analyses will be performed for gender (i.e., male, female or other) time since diagnosis (i.e., ≤ 3 years, > 3 years), type of cancer diagnosis (i.e., breast, colon or other), and type of treatment (i.e., locoregional therapy, systemic therapy or multimodal treatment). All analyses will be performed on an intention-to-treat basis. Per-protocol analyses will be carried out comparing participants in the intervention group who completed at least phase 1 of the intervention and had at least one meeting in phase 2 of the intervention, to participants in the control group.

We will use mixed-effects logistic regression to assess the primary outcome, paid employment [yes/no] at T1, T2, and T3. Odds ratios (ORs) with corresponding 95% confidence intervals (CIs) will be calculated to examine the effect of the intervention on the odds of paid employment.

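### The primary outcome and sample size concern one ever/never employment value per participant, but the primary analysis is a random-intercept logistic model of three interval answers, which estimates a different quantity

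*Protocol article*

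**What the plan says.** **Outcome.** The Primary outcome measure section states: "The primary outcome measure of this study is paid employment [yes/no] at any point during the 12-month follow-up". That is one value per participant. The data behind it are three interval answers: "Participants will be asked at T1–T3 whether they have worked in paid employment since the previous questionnaire". Table 2 describes the item in the same interval form: "Whether participant has engaged in paid employment since the last questionnaire [yes/no".

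**Sample size.** One proportion per arm from an earlier trial (30.8% v 10.5%) leads to the statement that "a total of 148 cancer survivors are required to detect the same difference of 20% between the two groups".

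**Analysis.** The Effect evaluation section plans mixed-effect regression "with participant as a random intercept will be conducted". For the primary outcome it says "We will use mixed-effects logistic regression to assess the primary outcome, paid employment [yes/no] at T1, T2, and T3", and then "Odds ratios (ORs) with corresponding 95% confidence intervals (CIs) will be calculated to examine the effect of the intervention on the odds of paid employment". Group allocation is the main independent variable in every model. On time it adds: "Additionally, the influence of time (T1, T2, T3) on the intervention’s effect will be examined (group*time interaction effect".

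No step in the article collapses the three answers into the ever/never value before the primary comparison.

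**The concern.** The outcome definition and the sample size ask what share of each arm obtained any paid work within a year. The model asks how the odds of a yes in a given interval differ between arms, conditional on a participant-level random effect, over intervals of 3, 3 and 6 months.

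A participant who finds a job in month 2 and keeps it answers yes three times. One who finds a job in month 10 answers yes once. Under the stated outcome each is one success; in the model they are not equal. The distinction matters here because the intervention aims at both early entry (the rapid job search principle in Table 1) and job maintenance (phase 3).

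There is also a scale problem. Employment tends to persist, so answers within a participant are strongly correlated, the random-intercept variance is large, and the conditional OR moves far from any OR computed on proportions. A reader who takes the published OR as the effect on the stated primary outcome could be badly misled.

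**Working it through.** **1. What the sample size refers to.** Two proportions, two-sided alpha 0.05, power 80%, 1:1, with continuity correction:

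n = [1.96·√(2p̄(1−p̄)) + 0.8416·√(p₁(1−p₁) + p₂(1−p₂))]² / d², then n_cc = (n/4)·[1 + √(1 + 4/(n·d))]².

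With p₁ = 0.308, p₂ = 0.108 (exactly 20 points), p̄ = 0.208 and d = 0.20:
- n = (1.125 + 0.468)² / 0.04 = 63.5
- n_cc = (63.5/4)·(1 + √1.315)² = 73.1, so 74 per arm and 148 in total

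This reproduces the stated 148, and 148/0.90 = 164.4 agrees with the stated 164 to rounding. The raw rates 30.8% v 10.5% give 142 with the correction. The figure belongs to a single ever/never comparison.

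**2. Effect on the stated outcome at the planning rates.**
- OR = (0.308/0.692) / (0.105/0.895) = 3.79
- Risk ratio = 0.308/0.105 = 2.93
- Risk difference = 20.3 points

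**3. What the planned model estimates on the same populations.** Assumptions:
- Entry into work has a constant hazard set so that ever-employment by 12 months is 30.8% and 10.5%. The 3-month entry probabilities are 1 − 0.692^(1/4) = 0.088 and 1 − 0.895^(1/4) = 0.027.
- A participant who answered yes answers yes again at the next questionnaire with probability s (persistence). The documents give no value, so s is varied.
- The model has a random intercept, time as categories and a group effect. It is fitted by maximum likelihood with numerical integration, without covariates.

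| Persistence s | Ever/never OR | Model OR (large sample) | Random-intercept SD |
|---|---|---|---|
| 0.3 | 3.79 | 4.0 | 1.2 |
| 0.5 | 3.79 | 5.4 | 1.9 |
| 0.7 | 3.79 | 9.3 | 2.8 |
| 0.8 | 3.79 | 14.8 | 3.5 |
| 0.9 | 3.79 | 36 | 4.8 |
| 0.95 | 3.79 | 98 | 6.2 |
| 0.98 | 3.79 | 418 | 8.2 |

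The marginal ORs at the separate visits stay between 3.3 and 3.8 throughout. A second fit gave about 4, 6, 11, 20, 57 and 192 for s from 0.3 to 0.95: the same direction and order of magnitude, with the exact size sensitive to the assumed histories.

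**4. Is it only a change of scale?** Set ever-employment to 30.8% in both arms, so the ever/never OR is 1.

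| What differs (intervention v control) | Model OR | Second fit |
|---|---|---|
| Persistence 0.9 v 0.5 | 1.44 | 1.6 |
| Persistence 0.5 v 0.9 | 0.70 | 0.63 |
| Entry earlier v later (entry hazard over the three intervals weighted 3:1:1 v 1:1:3, s = 0.9) | 2.49 | 2.0 |

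The model can show an effect in either direction where there is none on the stated outcome. The targets differ, not just the units.

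**5. At the planned size** (74 per arm, 150 simulated trials each):

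| s | Median model OR (IQR) | Median ever/never OR | Power, likelihood-ratio test of model | Power, ever/never z test |
|---|---|---|---|---|
| 0.5 | 5.3 (3.6–7.8) | 3.9 | 85% | 87% |
| 0.8 | 17.5 (8.2–41.4) | 3.7 | 84% | 86% |
| 0.9 | 37.6 (15.1–146.6) | 3.7 | 86% | 91% |

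The estimate becomes large and unstable, while power changes little.

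**The case against.** **The conditional OR is legitimate.** This stands. A reader might infer that the model's OR is inflated in the sense of biased. It is not: it consistently estimates a participant-specific effect under the model. The fault is that this is not the effect on the outcome the article declares.

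**The size depends on an assumption.** This also stands. Persistence is not in the documents, the estimator is not stated, and the fits omit the planned covariates. At persistence 0.3 the model OR (4.0) almost equals the ever/never OR (3.8). A many-fold gap is conditional on persistent employment, which is plausible for jobs but not documented.

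**Power.** A reader might infer that the trial loses power. The documents do not support that. Wald tests from such fits can do poorly when jobs are rarely lost (about 0.41 at 97% monthly retention in one simulation), but the article names no test statistic and likelihood-ratio power is close to that of the simple comparison.

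**The deciding contrast.** A reader might infer that the plan leaves open which test decides the trial. The text does rank the group effect first and treats the interaction as additional. What remains is whether the primary OR is overall or per visit, a detail that an analysis plan commonly settles.

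**First entry into work is analysed elsewhere.** The Kaplan–Meier, log-rank and Cox analyses of time until paid employment address it. They are secondary, so they reduce the mismatch without removing it.

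**T1–T3 might be meant cumulatively** (employed by 3, 6 and 12 months). Table 2 asks about the interval since the last questionnaire. A cumulative reading would also not help: persistence would then be exactly 1, the limit at which the random-intercept OR diverges.

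**Conclusion.** The point holds and should be corrected before analysis. The stated primary outcome and the sample size concern one ever/never proportion per arm; the stated primary model estimates a participant-specific OR over three intervals that also reflects job retention and timing of entry. The mismatch is in the current text and does not depend on any assumption.

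Its numerical size does. At the planning rates the model OR runs from about 4 (persistence 0.3), through about 15 to 20 (0.8), to over 90 (0.95 and above), against 3.8 for ever/never. With equal ever-employment it ranged from about 0.6 to 2.5 in the scenarios checked. The consequence is a headline estimate that can be misread, not a biased estimator or an underpowered trial.

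**What to change.** - **Primary analysis.** Derive one ever/never value per participant from the T1–T3 answers and the recorded job start dates. Compare the arms by logistic regression adjusted for the stratification factors (social benefit type and region), and report a standardised risk difference beside the OR.
- **Missing intervals.** State a rule for participants with a missing interval answer, for example multiple imputation. This is the real cost: the mixed model uses partial responders directly, a derived binary does not, and 10% loss to follow-up is planned for.
- **Secondary analysis.** Keep the T1–T3 repeated-measures model, with one named contrast and a marginal estimate (GEE, or standardised from the mixed model).
- **Leave the outcome definition as it is.** Counting only jobs started after randomisation would redefine the outcome, not correct its analysis. Paid work already held at T0 is a separate issue.

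No new data or participants are needed. The Trial status section expects results in 2026, so the change should be documented as an amendment before the allocation code is opened for analysis.

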### Randomization

Participants will be randomly allocated to either the intervention or CAU control group (1:1), using Castor EDC [27], stratified according to region in the Netherlands and social benefit type. The allocation sequence will be generated by the executing researcher ([name]) in Castor EDC. The sequence is concealed for everyone until participants are allocated. Neither the participant nor the research team and those delivering the intervention will be blinded to the randomization.

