#### IPS coaches

Certified IPS coaches, with a background in higher vocational education (e.g., social work) and a completed training from the Dutch IPS knowledge center “Phrenos,” will deliver the intervention. Additionally, they will receive a PLACES-training and guidance from a commercial organization specialized in reintegration after cancer (i.e., Re-turn). The PLACES-training includes two videos with information on cancer survivors’ unique problems and needs, information on the organization of cancer care, and on study-specific information. After this training, all coaches have the opportunity to ask questions and discuss uncertainties regarding the intervention or the study with the executive researcher ([name]). Also, intervision meetings will be held twice a year with all coaches to collectively discuss cases and to learn from one another. We aim to recruit coaches from various Dutch regions to ensure national coverage. Each coach will operate within their own region and use their existing extensive network of employers to find suitable jobs for participants. All coaches will be supported and monitored by the reintegration organization.

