#### Process evaluation

To assess the delivery and feasibility of the PLACES intervention, we will conduct a process evaluation using the model of Linnan and Steckler [37] (see Table 3). This model allows us to identify strengths and weaknesses of the intervention process that can be used to identify necessary improvements to enhance its effectiveness. Several key components of the intervention will be considered, including recruitment, reach, context, dose delivered, dose received, fidelity, and satisfaction.

**Table 3 Tab3:** Overview of process measures according to the model of Linnan and Steckler

Components	Topic	Method of assessment
Recruitment	1. Recruitment route (i.e., hospital, SSA, other) 2. Type of social benefit at baseline (i.e., partially work-disabled, fully work-disabled or on sick leave at the end of their employment contract)	At T0, participants will report the recruitment route and social benefit type. Percentages per recruitment route and type of social benefits will be calculated for all participants and separately for the intervention and control group
Reach	1. The number of people invited, screened and who eventually participated 2. Reasons for non-participation or drop-out 3. Reach of IPS coaches 4. Reach of hospitals	The research logbook reports on: - Invitation, screening and non-participation numbers, with a distinction per labor region (participant reach) - Reasons for nonparticipation or drop-out at baseline, during screening, and throughout the 12-month follow-up period (participant reach) - The number of IPS coaches and hospitals contacted, along with reasons and numbers of nonparticipation (reach of IPS coaches and hospitals) Reach of IPS coaches will additionally be determined by the percentage of participating IPS coaches relative to the total IPS coaches in the Netherlands Reach of hospitals will additionally be determined by the percentage of hospitals relative to the total hospitals with an oncology department in the Netherlands

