Differences between the intervention and control group in secondary outcomes will be analyzed using linear or generalized linear regression analyses. Effect sizes and their 95% confidence intervals will be reported for all outcomes. To analyze the secondary outcome “time until paid employment,” a Kaplan–Meier survival analysis will be performed, and differences between intervention and control group will be tested with the log-rank test. In addition, the Cox proportional hazard model, or accelerated failure time analysis if applicable, will be applied to estimate hazard ratios and the corresponding 95% CIs, and the median time until paid employment for the intervention and control group will be determined if possible. All statistical analyses will be conducted using the IBM SPSS Statistics 28.0 [39] or R statistical software version 4.1.3 [40], and the statistical significance will be determined at a two-tailed significance level of 0.05.

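### The log-rank test for time until paid employment names no strata; stratifying it by social benefit type would cost nothing and could recover a little power

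*Protocol article*

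**What the plan says.** - **Randomization:** allocation is 1:1, "stratified according to region in the Netherlands and social benefit type".
- **Effect evaluation, mixed-effects models:** because allocation was stratified on benefit and labour region, "they will be included as covariates in the model". The same paragraph adds that, in all models, "both unadjusted and adjusted models will be presented".
- **Effect evaluation, time until paid employment:** Kaplan–Meier curves are drawn and "differences between intervention and control group will be tested with the log-rank test". The text then continues: "In addition, the Cox proportional hazard model, or accelerated failure time analysis if applicable, will be applied to estimate hazard ratios", with 95% confidence intervals. No strata are given for the test and no covariates for the Cox model.
- **Table 3 (Process evaluation):** social benefit type at baseline has three levels: "partially work-disabled, fully work-disabled or on sick leave at the end of their employment contract".
- **IPS coaches:** "We aim to recruit coaches from various Dutch regions to ensure national coverage". The article does not give the number of regions used in randomisation.

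**The concern.** The article gives a rule for the stratification factors: they enter the analysis because they were used in allocation. It then chooses, for one outcome, a test to which that rule cannot apply as worded, and it does not say whether the test is stratified.

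This matters only if a factor is prognostic. Stratified allocation balances the arms within benefit type. If type also predicts time to work, a test that ignores it uses a variance that is too large for the balanced design, so it rejects less often than it should. The Context section ties the type of benefit to assessed work ability, so a prognostic effect is plausible. At stake is some power for time to return to work, which the article's strengths section presents as one of two core-set outcomes it covers.

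**Working it through.** **1. The plan's own figure.** The only sample size in the article is for the binary primary outcome: 80% power, alpha 0.05, total 148, raised to 164 for 10% loss. The planning rates are "30.8%; 95% CI 21.8–41.6 versus 10.5%; 95% CI 5.2–19.7, respectively". The figure reproduces with the continuity-corrected two-proportion formula at 31% v 11%:
- n′ = [1.96·√(2·0.21·0.79) + 0.8416·√(0.31·0.69 + 0.11·0.89)]² / 0.20² = 63.9
- n = (n′/4)·[1 + √(1 + 4/(n′·0.20))]² = 73.6, so 74 per arm and 148 in total
- 148/0.9 = 164.4

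No events or power are stated for the log-rank test, so there is no figure there to contradict.

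**2. What the planning rates imply for the log-rank test.** Under proportional hazards:
- HR = ln(1 − 0.308)/ln(1 − 0.105) = 3.32
- Expected events with 82 per arm = 82 × (0.308 + 0.105) = 33.9
- Schoenfeld power = Φ(√33.9 × ln 3.32/2 − 1.96) = 0.94. With 74 per arm there are 30.6 events and the power is 0.91.

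**3. Plain v stratified test, by simulation.** From the document: 164 participants, 1:1 allocation, 12-month follow-up, two-sided 0.05, 10.5% control rate. Assumed: three equal benefit types, permuted blocks of 4 within type, exponential times, a constant hazard ratio within type, and the hazard pattern across types. There were 4,000 trials per setting, with Monte Carlo standard error of about 0.003 to 0.008. The second control rate (30%, HR 1.9) is also an assumption. Without a prognostic effect it gives an intervention rate of 1 − 0.70^1.9 = 49%, a difference close to the planned 20 points.

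| Control rate, HR | Hazards across types | Power, plain | Power, stratified by type |
|---|---|---|---|
| 10.5%, 3.3 | equal | 0.909 | 0.909 |
| 10.5%, 3.3 | 1:2:4 | 0.89 | 0.91 |
| 10.5%, 3.3 | 1:3:9 | 0.87 | 0.90 |
| 30%, 1.9 | equal | 0.724 | 0.723 |
| 30%, 1.9 | 1:2:4 | 0.66 | 0.71 |
| 30%, 1.9 | 1:3:9 | 0.58 | 0.70 |

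When type was prognostic, the plain test's size was 0.033 to 0.048 and the stratified test's 0.047 to 0.059. A repeat run gave gains of 1 to 3 points at the planned rates and 6 to 13 points at the 30% control rate. It showed no difference without a prognostic effect (0.916 v 0.915; 0.717 v 0.717), and the plain test's size was 0.030 to 0.047 when type was prognostic.

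**4. Effect of the number of strata.** A further simulation used 148 participants and the planned rates, and stratified on every cell. Three benefit types were crossed with an assumed 1, 2, 4 or 10 regions, and the log-hazard SD between cells was varied. For scale, the 1:2:4 pattern has an SD of ln 2 × √(2/3) = 0.57 and the 1:3:9 pattern ln 3 × √(2/3) = 0.90.

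| Strata | SD 0, plain v stratified | SD 0.5 | SD 1.0 |
|---|---|---|---|
| 3 | 87.1 v 87.4% | 86.5 v 87.7% | 79.6 v 86.3% |
| 6 | 87.4 v 87.3% | 86.0 v 87.2% | 83.4 v 86.7% |
| 12 | 88.5 v 87.9% | 87.4 v 87.8% | 82.0 v 86.9% |
| 30 | 88.3 v 85.9% | 87.4 v 85.7% | 82.1 v 83.2% |

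The plain test's size was 4.8 to 5.1% at SD 0 to 0.5 and 3.6 to 3.9% at SD 1.0. With 30 strata there is about one event per cell (30.6/30). Cells that hold only one arm add nothing, so stratifying on all of them loses 2 points when prognosis is weak or absent.

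**The case against.** A reader might infer that the plan commits to an unstratified test, contradicts its own stratification rule, and is therefore conservative and underpowered. The documents do not support that reading.

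- **Not stated as unstratified.** That is the ordinary reading of a log-rank test given without strata, but it is drawn from silence. A condensed article may leave such strata to the analysis plan.
- **No contradiction.** The covariate rule is written for regression models, and a log-rank test is not one.
- **The Cox model may already be covered.** The wording about unadjusted and adjusted versions of all models can fairly be extended to it, and a log-rank test followed by Cox is a conventional pairing. Still, the Cox sentence lists no covariates. If the model is adjusted, its hazard ratio will sit beside a p-value from a test that may not be.
- **The loss is conditional.** Nothing in the article says how prognostic benefit type is, how participants are spread across types, or how many regions there are. The largest gap above (0.58 v 0.70) rests on a control rate, hazard ratio and hazard spread that are all assumed.
- **Validity is not harmed.** A conservative test does not inflate type I error, and the outcome is secondary.

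All of this stands and limits the point to an improvement. One further objection is that stratifying can itself cost power. That applies to many sparse region-by-type cells, not to three benefit types, where no penalty appeared even without a prognostic effect.

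**Conclusion.** The point holds as a minor, free improvement. The article names a log-rank test without strata for an outcome whose randomisation was stratified. If benefit type is prognostic, a plain test gives away about 1 to 3 points of power at the planned rates under 1:2:4 or 1:3:9 hazards, and about 5 to 13 points at an assumed 30% control rate. If type is not prognostic, nothing is lost. These sizes rest on equal benefit types, blocks of 4, proportional hazards within type and the assumed hazard patterns. They also assume that randomisation used the three benefit levels listed in Table 3. The direction of the effect does not depend on the exact values; its size does.

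**What to change.** Amend the sentence to say that time until paid employment will be tested with a log-rank test stratified by social benefit type (three levels), and that the Cox model will be stratified by benefit type, or adjusted for it, with region as a covariate. If an accelerated failure time model is used instead, it should carry both factors as covariates. Do not stratify the log-rank test on region by type where cells are sparse.

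The cost is one sentence and no new data, ideally settled before the data are analysed. Region then enters only through the model and not the test, which is a reasonable trade while the number of regions is unstated and may be large.
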